## Abstract

**Introduction:**

Shoulder pain is a debilitating musculoskeletal condition with functional, physical, and psychological impacts. Interventions for chronic shoulder pain should address the biopsychosocial model, with Cognitive Functional Therapy (CFT) emerging as a promising physiotherapy approach. CFT approaches the multidimensional nature of pain, integrating physical and cognitive aspects. To date, no study has assessed the effectiveness of CFT in individuals with chronic shoulder pain. Therefore, this randomized controlled trial aims to compare the effects of CFT to therapeutic exercises on pain intensity, disability, self-efficacy, sleep quality, biopsychosocial aspects, and central pain processing in individuals with chronic shoulder pain.

**Methods:**

This will be a randomized controlled trial, single-blinded with two parallel groups. Seventy-two individuals with chronic shoulder pain will be randomly assigned to one of two groups: CFT or Therapeutic exercise. The interventions will last 8 weeks, with the CFT group receiving therapy once a week and the therapeutic exercise group receiving sessions twice a week. The primary outcomes will be pain intensity and disability, while the secondary outcomes will include function, self-efficacy, sleep quality, biopsychosocial factors, perception of improvement/deterioration, and central pain processing. The outcome measures will be assessed at baseline, 4^th^ week, end of treatment (8^th^ week), and 12^th^-week follow-up.

**Conclusion:**

The results of this study will contribute to understanding the effectiveness of CFT in treating individuals with chronic shoulder pain.

**Trial registration number:**
NCT06542666

## Introduction

Chronic shoulder pain has an estimated annual prevalence ranging from 0.7% to 55.2% in the general population [1]. It affects 45% of individuals engaged in repetitive work-related movements [2], pointing to an annual incidence of 37.8 per thousand people. Shoulder pain has significant physical, social, and psychological impact, often contributing to work limitations and difficulties in daily activities. This results in a significant economic burden on society due to the use of medication, sick leave, medical, and hospital expenses [3]. Furthermore, approximately 50% of individuals with shoulder pain continue to experience persistent pain after one year [4], indicating a high likelihood of chronification.

The condition is also linked to functional impairment and psycho-emotional distress, including depression, anxiety, decreased quality of life, kinesiophobia, catastrophizing, and low self-efficacy [3,5,6]. Thus, chronic shoulder pain presents multifactorial characteristics connecting the painful experience to fear-avoidance behaviors, which can further reduce function [6,7]. Therefore, interventions for individuals with chronic shoulder pain should align with the biopsychosocial model [8,9].

Therapeutic exercises are the primary recommendation for the treatment of shoulder pain [10–12]. These exercises typically focus on joint mobility, muscle stretching, and strengthening, often targeting the scapulothoracic and glenohumeral muscles [10,13,14]. However, given the strong association between psychosocial factors and the prognosis of chronic shoulder pain [5,15], exercise therapy alone may not adequately address the multidimensional nature of pain, as it fails to target the psychosocial aspects. This emphasizes the need for interventions that encompass physical, emotional, and behavioral components to yield more relevant and effective outcomes [16].

Cognitive Functional Therapy (CFT) is a patient-centered, individualized approach to address physical, psychological, emotional, and lifestyle barriers to improve pain symptoms, disability, and maladaptive cognitive-behavioral factors [17,18]. The CFT is structured into three phases: (1) making sense of pain, (2) exposure with control, and (3) lifestyle changes [19–21], including an approach for improving physical activity and sleep quality. Sleep has an important role in modulating physical and psychological health. Disruptions to sleep have been shown to significantly diminish quality of life and exacerbate the experience of pain in individuals with musculoskeletal conditions [22,23]. By contrast, physical activity has been identified as a key factor in promoting health, diminishing pain, and improving sleep quality, thereby influencing recovery and pain management outcomes [22,23]. Previous studies have demonstrated the positive effects of CFT on pain intensity, disability, and psychological factors in individuals with chronic low back pain [20,24–27], neck pain [28,29], and knee osteoarthritis [30]. Although CFT has shown significant and positive results for the treatment of chronic pain in other musculoskeletal conditions, randomized controlled trials investigating the application of CFT to treat chronic shoulder pain have not yet been conducted.

Therefore, this study aims to compare the effects of CFT with therapeutic exercise on biological aspects of pain (pain intensity, disability, function, perception of improvement/deterioration, and central pain processing), and psychosocial aspects of pain (sleep quality, self-efficacy, and biopsychosocial factors). We hypothesize that CFT will lead to greater improvements in these outcomes compared to therapeutic exercise.

## Methods

### Study design

This study is a randomized controlled trial with a superiority design, single-blinded with two parallel groups. Outcome assessors will be blinded to participants’ assigned treatment groups. This protocol follows the Standard Protocol Items: Recommendations for Interventional Trials (SPIRIT) statement and checklist [31]. This study was prospectively registered at clinicaltrials.gov (NCT06542666) and The World Health Organization data set is described in **Table 1**. The authors confirm that all ongoing and related trials for this intervention are registered.

**Table 1 pone.0320025.t001:** World Health Organization trial registration data set.

Data category	Information
Primary registry and trial identifying number	NCT06661681
Date of registration in primary registry	23/07/2024
Primary sponsor	Federal University of Paraíba
Contact for public queries	[contact]
Contact for scientific queries	[name],
Public title	Cognitive Functional Therapy for Chronic Shoulder Pain
Scientific title	Cognitive Functional Therapy versus therapeutic exercises for the treatment of individuals with chronic shoulder pain: A protocol for a randomized controlled trial
Countries of recruitment	Brazil
Health condition(s) or problem(s) studied	Chronic Shoulder Pain; Exercise Therapy; Psychosocial Rehabilitation
Intervention(s)	Cognitive Functional Therapy and Therapeutic Exercises
Key inclusion and exclusion criteria	Inclusion Criteria: men and women; age between 18 and 60 years; presence of shoulder pain for more than 3 months; pain intensity of 4 points or more on the 11-point Numeric Pain Rating Scale during the past week; high level of disability or moderate irritability. Exclusion Criteria: history of fracture or surgery of the clavicle, scapula, and/or humerus, surgical stabilization or rotator cuff repair; history of dislocation, instability (positive sulcus sign or apprehension test), and/or rotator cuff tear (positive drop arm test); adhesive capsulitis verified by the presence of gradual onset pain associated with stiffness and reduced passive and active mobility; ongoing pregnancy; reproduction of shoulder pain radiating to the entire upper limb during cervical or thoracic spine tests (positive Spurling test); neurological or systemic diseases that may alter muscle strength and sensitivity such as rheumatoid arthritis, fibromyalgia, lupus, gout, and diabetes; corticosteroid injection in the shoulder region in the last 3 months; physiotherapy treatment in the last 6 months.
Study type	Interventional
Date of first enrollment	February 14, 2025
Target sample size	72
Recruitment status	Not yet recruiting
Primary outcome(s)	Pain intensity and disability
Key secondary outcomes	Self-efficacy, Sleep quality, Biopsychosocial aspects, Central pain processing

### Research site

The evaluation and intervention procedures of this study will be conducted at the Laboratory for the Study of Balance, Dynamometry, and Electromyography and at the Physiotherapy School Clinic of the Universidade Federal da Paraíba, Brazil, in 2025.

### Sample

The study will include adults aged between 18 and 60 who report shoulder pain lasting at least 3 months. They should rate their shoulder pain 4 or higher on the 11-point Numerical Pain Rating Scale (NPRS) over the past week [32], and high level of disability (Shoulder Pain and Disability Index score ≥ 47) [33,34] or moderate irritability according to Staged Approach for Rehabilitation Classification: Shoulder Disorders (STAR–Shoulder) [35,36].

Non-inclusion criteria will be apply to individuals with: a history of fracture or surgery of the clavicle, scapula and/or humerus; surgical stabilization or repair of the rotator cuff; a history of dislocation, instability (positive Groove Sign or Seizure Test) and/or rotator cuff rupture (positive Arm Drop Test); adhesive capsulitis verified by the presence of pain with gradual onset associated with stiffness and reduced passive and active mobility; reproduction of pain in the shoulder that radiates to the entire upper limb, ongoing pregnancy; tingling or numbness in the upper limb or any other symptom in the upper limb during tests on the thoracic or cervical spine (Positive Spurling Test); systemic disease or neurological condition that can alter muscle strength and sensitivity, such as fibromyalgia, rheumatoid arthritis, gout, lupus, diabetes and/or stroke; physiotherapy treatment for shoulder pain in the previous 3 months, corticosteroid injection in the shoulder region in the last 3 months, and active treatment for cancer [37–39], impairments in sensation, blood clotting disorders, and/or contraindications to the application of ice.

Individuals with surgeries, fractures, musculoskeletal or neurological conditions preventing them from accessing treatment, or those who received corticosteroid injections in the shoulder region during the treatment or follow-up period will be discontinued from the study.

The sample size was calculated using the SampSize App (https://app.sampsize.org.uk/) and the following formula described by Flight et al (2015) [40]:

$$n=\frac{\left(r+1\right){\left(Z_{1-\beta }+Z_{1-\frac{\alpha }{2}}\right)}^{2}\sigma^{2}}{rd^{2}}$$

The calculation was based on an estimated mean difference of 18 points [41] (standard deviation of 24.6) [42] in shoulder disability, assessed with Shoulder Pain and Disability Index (SPADI), with a two-tailed significance set at 0.05, power at 80%, and accounting for a 15% dropout, which resulted in 36 individuals per group for a total of 72 individuals. The sample size, calculated based on pain intensity (a mean difference of 2 points and a standard deviation of 2.5 on the NPRS), resulted in a total sample of 48 individuals. Therefore, the sample size calculation for this study was based on shoulder disability.

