### Procedures

Baseline assessments will include the characteristics of the participants, such as sociodemographic data (e.g., sex of birth, age, height, weight, body mass index, occupation, education level, upper limb dominance, physical activity characteristics) as well as information related to shoulder pain (e.g., painful side, duration of symptoms, pain intensity, use of medication, influence of pain on work, leisure activities, and sleep, and details of previous treatments). The self-reported most painful shoulder will be considered for all outcome measures for individuals with bilateral symptoms. Outcome measures will be assessed at baseline, 4-week, at the end of treatment (8-week), and 12-week follow-up, except patients’ expectations of treatment, which will be measured only at baseline, and perception of improvement/deterioration, which will be measured at 4-week, 8-week, and 12-week follow-ups (Fig 2). Patients’ treatment expectations will be assessed using the question “How much do you expect your shoulder to improve at the end of treatment?”. The score will be measured on a 7-point Likert scale, where 1 corresponds to “the worst possible” and 7 corresponds to “fully recovered”. This assessment will be conducted before the intervention begins. Patient expectations are a significant predictor of treatment outcomes, as demonstrated by a study evaluating individuals with shoulder pain [43].

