
### Interventions

The interventions will last for 8 weeks, as individuals treated during this time frame have shown statistically and clinically significant improvements in previous research involving CFT [17,27] or therapeutic exercises for shoulder pain [12,13,67]. The CFT group will have one session per week, while the therapeutic exercise group will have two sessions per week. All treatment sessions will be supervised by a physiotherapist with 15 years of experience. Adherence to treatment sessions and assessments will be encouraged verbally at each session and through text messages sent the day before the scheduled appointment. In the event of absence, contact will be made by telephone to identify the reason for the absence and reschedule the session. Each session for both groups will last approximately 40–60 minutes.

Information regarding adverse effects, use of ice, heat, medication for pain, or protocol deviations reported by participants will be collected at all appointments by the physiotherapist responsible for administering the treatment and documented in the study report. An individual’s allocated intervention will be discontinued if they experience significant adverse effects related to the intervention or if they request to withdraw. The decision to discontinue the intervention will be made by the research team in a shared decision with the individual.

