### Data analysis

Statistical analysis will be conducted using the Statistical Package for the Social Sciences (SPSS) version 24.0 or a more recent version (SPSS Inc., Chicago, IL). Continuous data will be summarized as means ± standard deviation (SD) and 95% confidence intervals (CIs). Data normality will be assessed through visual inspection of histograms and the Shapiro-Wilk test. The analysis will adhere to the intention-to-treat principle. Between-group differences (treatment effects) and their corresponding 95% CIs will be computed using linear mixed models with Bonferroni adjustments. If non-normality of the data is identified, transformations will be performed as needed or generalized linear mixed models will be considered. Fixed effects will include group, time, and the group-by-time interaction. Random effects will account for individual variability. A significance level of 0.05 will be applied for all statistical tests.

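### Discontinuing participants from the study after a shoulder corticosteroid injection conflicts with the stated intention-to-treat analysis and may lose later outcomes informatively

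*Protocol article*

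**What the plan says.** Three statements in the protocol article bear on this.

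- **Sample.** For injections: "those who received corticosteroid injections in the shoulder region during the treatment or follow-up period will be discontinued from the study". The other half of the same sentence covers "Individuals with surgeries, fractures, musculoskeletal or neurological conditions preventing them from accessing treatment". The injection clause carries no qualifier. The surgery and fracture clause appears to be limited to cases that block access to treatment.
- **Interventions.** A separate rule says that a participant's "allocated intervention will be discontinued if they experience significant adverse effects related to the intervention or if they request to withdraw". This stops the treatment and does not mention the study.
- **Data analysis.** "The analysis will adhere to the intention-to-treat principle". The method is a linear mixed model: "Fixed effects will include group, time, and the group-by-time interaction".

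The abstract states that "The primary outcomes will be pain intensity and disability". Under Procedures, "Outcome measures will be assessed at baseline, 4-week, at the end of treatment (8-week), and 12-week follow-up". Treatment lasts 8 weeks, so week 12 falls four weeks after it ends. The article does not say that assessments continue after an injection, surgery or fracture.

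**The concern.** Intention-to-treat needs outcomes, as far as they can be obtained, from everyone randomised, whatever happens afterwards. A rule that ends study participation because of an event after randomisation works against that. The loss would be created by the protocol itself, on top of ordinary dropout.

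The reason for the loss also matters. Participants enter with pain of at least 4 on the NPRS and either high disability or moderate irritability. An injection during the trial is plausibly sought because pain has not settled. If so, the missing later visits come disproportionately from poor responders. Participants know their treatment, and the arms differ in contact (one session a week against two), so the number of injections could differ between arms. The week-8 and week-12 differences in pain and disability would then shift in favour of the arm that lost more participants.

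**Working it through.** **1. Can the Sample rule mean only stopping treatment?** The Interventions section has its own wording for stopping the allocated intervention, whereas the Sample section refers to the study. The Sample rule also covers the follow-up period. Between weeks 8 and 12 there is no treatment left to stop, so the rule can only affect the week-12 assessment. The treatment-only reading does not fit.

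**2. The plan's own sample size.** Inputs from the Sample section: difference 18, SD 24.6, two-sided 0.05, power 80%, dropout 15%, equal arms.

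n per arm = 2 × (1.960 + 0.842)² × 24.6² / 18² = 29.3, rounded up to 30. Then 30 / 0.85 = 35.3, rounded up to 36 per arm, 72 in total. The stated figure is reproduced.

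**3. Power.** Power = Φ(18 / SE − 1.96), with SE = 24.6 × √(2/n).

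| Loss | n per arm | SE | Power |
|---|---|---|---|
| 0% | 36 | 5.80 | 87.4% |
| 15% | 30.6 | 6.29 | 81.7% |
| 20% | 28.8 | 6.48 | 79.3% |
| 25% | 27 | 6.70 | 76.7% |

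Enforced removals draw on the same 15% allowance as ordinary dropout.

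**4. Size of the shift, observed cases.** The protocol gives no event rates, so the removal counts are assumptions. If the worst fraction p of an arm is removed exactly by week-12 score, the mean of those left falls by 24.6 × φ(z) / (1 − p), where z is the 1 − p normal quantile.

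- 4 of 36 removed: p = 0.111, z = 1.221, φ = 0.1894, fall 5.24 points.
- 1 of 36 removed: p = 0.028, z = 1.915, φ = 0.0638, fall 1.61 points.
- Difference between arms: 5.24 − 1.61 = 3.63 points.

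**5. Size of the shift, planned model.** Suppose m visits before the event are kept and any two visits correlate at 0.6. Those visits then explain a share m × 0.6² / (1 + (m − 1) × 0.6) of the week-12 variance. For m = 2 this is 0.72 / 1.6 = 0.45. For m = 3 it is 1.08 / 2.2 = 0.49. The model therefore leaves about 0.51 to 0.55 of the observed-case shift.

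**6. Check by simulation.** 36 per arm, SD 24.6, compound symmetry at 0.6 with the covariance taken as known, and 6,000 trials per scenario. Removal was by worst week-12 score, either exact or blurred by noise of 0.5 or 1 SD. Either week 12 alone or weeks 8 and 12 were lost.

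| Removals (one arm v other) | Observed cases | Mixed model |
|---|---|---|
| 4 v 1, exact | 3.55 | 1.82 to 1.95 |
| 4 v 1, noise 0.5 SD | 3.2 | 1.6 to 1.8 |
| 4 v 1, noise 1 SD | 2.5 | 1.3 to 1.4 |
| 2 v 1, all settings | 0.9 to 1.3 | 0.5 to 0.7 |
| 2 v 2, all settings | about 0 | about 0 |

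Shifts are in SPADI points and favour the arm with more removals. Exchanging the arms reverses the sign.

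**The case against.** The strongest reply is that the effect is small and its size unknown. No injection rate is given, the exposure is 12 weeks with eight under supervised treatment, and 4 against 1 is an unfavourable choice. Equal removal leaves the mean difference essentially unbiased. The planned mixed model halves the shift. Power is largely protected too: five removals are 5 / 72 = 7%, inside the 15% allowance. All of this stands, and it limits the severity.

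Four stronger readings are tempting, and the protocol does not support them.

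- *That outcomes already collected are deleted.* The text does not say so. Visits before the event can stay in the mixed model, and only later visits are at risk.
- *That surgery and fracture raise the same problem as injection.* Those events appear to be limited to cases preventing access to treatment, and a fracture is not in itself a sign of uncontrolled shoulder pain. The argument about informative loss rests mainly on the injection clause.
- *That the Sample and Interventions rules contradict each other.* They address different triggers. The conflict is between Sample and Data analysis.
- *That the data are certainly missing not at random and the model is useless.* Informative loss is plausible but not shown, and earlier visits recover about half of the shift in this illustration.

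It can also be said that handling of such events belongs in an analysis plan that is not shown. That holds for the choice of sensitivity analyses. It does not hold for the discontinuation rule: this is stated in the protocol and governs data collection, and no analysis plan can recover questionnaires that were never given.

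**Conclusion.** The point holds in a limited form, as a should-fix. A rule that discontinues participants from the study after a shoulder injection conflicts with the intention-to-treat commitment, and its reach into follow-up rules out reading it as stopping treatment only. That later outcomes would go uncollected is the natural reading of the wording, although the article does not spell it out.

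Under the planned model, the illustrative shift is about 1.3 to 1.9 SPADI points at 4 against 1 removals. That is 7% to 11% of the 18-point design difference and at most about a third of the 5.80-point standard error (1.9 / 5.80 = 0.33). At 2 against 1 it is about 0.5 to 0.7, and with equal removals about 0. These figures rest on assumed removal counts, a within-person correlation of 0.6, the protocol's SD of 24.6, and removal driven by the week-12 score. The direction cannot be known in advance. The conflict between the two sections does not depend on any of these assumptions.

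**What to change.** Amend the Sample section so that it agrees with Data analysis:

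1. Separate stopping the allocated intervention from leaving the study. This takes no position on whether treatment should continue after any of these events.
2. State that the remaining scheduled week 4, 8 and 12 assessments continue after an injection, surgery, fracture or other listed condition unless the participant withdraws consent.
3. Record the event and its date.
4. Analyse all randomised participants in the group to which they were allocated.

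The cost is a wording amendment, submitted to the ethics committee and registry as the protocol already requires, plus assessments that are already scheduled. The sample size stays at 72. The small downside is that the treatment difference will then include any effect of the co-treatment. A sensitivity analysis excluding data after the event can examine that, and it can be specified in the analysis plan.

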### Recruitment

The recruitment of the individuals will be carried out between February 2025 and June 2026. Participants will be recruited through flyers posted in university buildings, orthopedic and rheumatology clinics, public places, and community health clinics in João Pessoa. Recruitment strategies will also include online advertisements (e.g., social media) and the personal and professional networks of the researchers involved in the study.

